### Treatment days

Tables 1 and 2 illustrate the treatment schedule and sequence of enrollment, follow-up and interventions, based on the SPIRIT-guidelines for publication of trial protocols.

**Table 1 Tab1:** Schedule for Screening and follow-up of the ALA-RDT in GBM study

	Screening for cohorts 0 and 1	Screening for cohorts 2 to 8	Follow-Up 1 (all patients)	Follow-Up 2 (all patients)
Day	-7 to -4 before surgery	-14 to -2 before first RDT	12 weeks after firstadjuvant RT	6 months after firstadjuvant RT
**Informed consent**:	X	X		
**In- / Exclusion criteria**:	X	X		
**MRI**:	MRI outside screening period used for diagnosis and as baseline value	MRI up to 72 h after surgery, performed outside study protocol Screening period used for diagnosis and baseline	X	X
**Medical and neurological examination**	X	X	X	X
**Laboratory panel**	X	X	X	X
**Medical / surgical history**	X	X		

**Table 2 Tab2:** Schedule for procedures of the ALA-RDT in GBM study

		Neoadj. RT		Surgery		Adjuvant RT (beginning 2–6 weeks as clinically indicated after surgery)																				
		*(pre)OP*					*1. week*					*2. week*					*3. week*					*4. week*				
		*Treatment Day*																								
**Cohort**	**Intervention**	*-3*	*-2*		*0*		*1*	*2*	*3*	*4*	*5*	*6*	*7*	*8*	*9*	10	*11*	*12*	*13*	*14*	*15*	*16*	*17*	*18*	*19*	*20*
**0**	RT with 1.8 Gy	X	X				X	X	X	X	X	X	X	X	X	X	X	X	X	X	X	X	X	X	X	X
	Surgery of rGBM				X																					
	5-ALA before RT (RDT)						X																			
**1**	RT with 1.8 Gy	X	X				X	X	X	X	X	X	X	X	X	X	X	X	X	X	X	X	X	X	X	X
	Surgery of rGBM				X																					
	5-ALA before RT (RDT)	X																								
**2**	RT with 1.8 Gy						X	X	X	X	X	X	X	X	X	X	X	X	X	X	X	X	X	X	X	X
	Surgery of rGBM				X																					
	5-ALA before RT (RDT)						X					X														
**3**	RT with 1.8 Gy						X	X	X	X	X	X	X	X	X	X	X	X	X	X	X	X	X	X	X	X
	Surgery of rGBM				X																					
	5-ALA before RT (RDT)						X					X					X									
**4**	RT with 1.8 Gy						X	X	X	X	X	X	X	X	X	X	X	X	X	X	X	X	X	X	X	X
	Surgery of rGBM				X																					
	5-ALA before RT (RDT)						X					X					X					X				
**5**	RT with 1.8 Gy						X	X	X	X	X	X	X	X	X	X	X	X	X	X	X	X	X	X	X	X
	Surgery of rGBM				X																					
	5-ALA before RT (RDT)						X			X		X					X					X				
**6**	RT with 1.8 Gy						X	X	X	X	X	X	X	X	X	X	X	X	X	X	X	X	X	X	X	X
	Surgery of rGBM				X																					
	5-ALA before RT (RDT)						X			X		X			X		X					X				
**7**	RT with 1.8 Gy						X	X	X	X	X	X	X	X	X	X	X	X	X	X	X	X	X	X	X	X
	Surgery of rGBM				X																					
	5-ALA before RT (RDT)						X			X		X			X		X			X		X				
***8***	RT with 1.8 Gy						X	X	X	X	X	X	X	X	X	X	X	X	X	X	X	X	X	X	X	X
	Surgery of rGBM				X																					
	5-ALA before RT (RDT)						X			X		X			X		X			X		X			X	

### Toxicity assessment

All patients will be hospitalized for the course of treatment procedure and receive daily AE/SAE-monitoring. Physical and neurological examinations will be performed routinely on a weekly basis and laboratory panels for toxicological safety will be drawn before every RDT-fraction, but also at least weekly. Toxicity will be monitored daily and classified according to CTCAE Vers. 5.0. All serious adverse events will be immediately reported to the Data Safety Monitoring Board.

### Follow-Up

All patients will receive a six-week follow-up after the end of radiotherapy to evaluate sequential side effects of repeated administration of 5-ALA. Additional follow-ups, including MRI-scans, will be performed twelve weeks and six months after the beginning of adjuvant treatment.

### End-points

Primary: To determine the maximum tolerated dose and safety of (neo)adjuvant RDT. MTD is defined as maximum dose level before two or more patients suffer from DLT.

Secondary: To evaluate six-months overall survival rate (OSR), six-months progression-free survival rate (PFSR) and six-months event-free survival rate (EFSR), as well as histological tissue changes after neoadjuvant treatment. OSR, PFSR and EFSR will be determined from study inclusion to the second follow-up, six months after the beginning of adjuvant treatment.

Exploratory: To explore concentration changes of 5-ALA metabolites in urine samples and changes of radiobiological marker concentration in blood serum samples.

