## Methods

### Trial design, setting and recruitment

This is a prospective, single-armed, single center phase I/II dose escalation-study, based in the University Hospital of Münster, Germany. The aim of the study is to determine the maximum tolerated dose (MTD) and safety of repeated application of oral 5-ALA as a radiosensitizer during (neo)adjuvant radiotherapy for the treatment of glioblastoma recurrence. All patients will receive 36 Gy adjuvant RT in 20 fractions. An increasing number of RT-fractions will be conducted as radiodynamic therapy (RDT), which will consist of 1.8 Gy-irradiation 7–9 h after oral application of 20 mg/kg bodyweight 5-ALA in a tap-water-solution.

Recruitment will start in cohort 0 with one RDT-fraction and patients will be allocated consecutively to this and the following cohorts, which will be numbered sequentially from 0 to 8. Each cohort encompasses three initial patients being expanded by additional three participants in case of a dose limiting toxicity (DLT), following a 3 + 3-design. With increasing cohort number, the quantity of RDT-fractions will be increased by one with a maximum of eight adjuvant applications in cohort 8. Additionally, in cohorts 0 and 1, patients will receive two neoadjuvant RT-fractions (in case of cohort 1, the first fraction will be conducted as RDT). In these cohorts, a decisive histopathological analysis of the resected tissue will account for changes induced by neoadjuvant therapy. MDT is considered to be reached in case of DLT in two or more patients on the same dose level. A study continuation with the next dose-level will be evaluated and approved by the data safety and monitoring board (DSMB) after a six-week follow-up of the last RT-fraction of the last patient within a cohort. The study started recruitment with the first patient in Q1 2023 with an estimated study duration of 30 months.

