#### Blood and tissue samples

Tissue sampling and evaluation of morphological changes in brain tissue will be performed on cohorts 0 and 1 after neoadjuvant treatment. These analyses will therefore include tissue changes after sole RT (cohort 0) as well as RDT (cohort 1), based on parameters like Caspase-3, IBA1, H&E, EvG, P53, Ki67 and gammaH2AX. Blood samples will be drawn for safety clearance as part of toxicity assessment and to monitor changes of ALA-metabolites in serum (PPIX) before every application of 5-ALA. Additional blood samples for analysis of concentration changes in radiobiological markers (including markers like IL-6, IL-8, TNF-Alpha and VEGF) will be drawn during neoadjuvant treatment (day − 3 and day − 2) and at the beginning (day 1 and day 2) and end (day 20) of adjuvant treatment.

Concentration changes of 5-ALA-metabolites in urine samples will be evaluated during neoadjuvant treatment (day − 3) and surgery (day 0) for cohorts 0 and 1 and at the beginning (day 1) and first follow-up for all study participants.

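### The primary objective claims an MTD of (neo)adjuvant RDT, but only adjuvant RDT is escalated; the single neoadjuvant fraction in cohort 1 supports no more than a pass/fail safety check

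*Protocol article*

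**What the plan says.** The protocol article states the scope of the primary objective in three places.

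- **End-points:** "Primary: To determine the maximum tolerated dose and safety of (neo)adjuvant RDT". The same section adds: "MTD is defined as maximum dose level before two or more patients suffer from DLT".
- **Trial design, setting and recruitment:** the aim is the MTD and safety of "repeated application of oral 5-ALA as a radiosensitizer during (neo)adjuvant radiotherapy for the treatment of glioblastoma recurrence".
- **Abstract, Methods:** the primary endpoint is the MTD of repeated 5-ALA administration, with no mention of the neoadjuvant setting.

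The trial design section describes the escalation as "With increasing cohort number, the quantity of RDT-fractions will be increased by one with a maximum of eight adjuvant applications in cohort 8". Cohorts 0 and 1 also receive two radiotherapy fractions before surgery, and "in case of cohort 1, the first fraction will be conducted as RDT". The section on blood and tissue samples confirms that cohort 0 has radiotherapy alone before surgery. Cohorts have three patients and grow to six only after a DLT.

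The neoadjuvant part is given two purposes: histology of the resected tissue (trial design, tissue samples and secondary endpoints) and early detection of excessive tissue reactions (Discussion).

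**The concern.** An MTD is a statement about a ladder: a level was tolerated and the next level up was not, or the top was reached. For the label to cover neoadjuvant RDT, the neoadjuvant dose would have to vary across levels. Here it takes one positive value, in one cohort.

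The article presents the trial as the first evaluation of repeated 5-ALA as a radiosensitizer in humans, and it foresees further evaluation if results are positive. A result labelled as the MTD of (neo)adjuvant RDT could be taken to cover RDT before surgery, or before and after surgery, at fraction numbers that no patient received in that setting.

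**Working it through.** The plan gives no numerical figure for this point, so there is none to reproduce. The check is a count from Table 2, followed by the possible outcomes under the MTD definition and the precision of cohort 1.

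**1. RDT fractions per cohort (Table 2)**

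| Cohort | Neoadjuvant RDT | Adjuvant RDT |
|---|---|---|
| 0 | 0 | 1 |
| 1 | 1 (day -3) | 0 |
| 2 | 0 | 2 |
| 3 | 0 | 3 |
| 4 | 0 | 4 |
| 5 | 0 | 5 |
| 6 | 0 | 6 |
| 7 | 0 | 7 |
| 8 | 0 | 8 |

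The 5-ALA given before anaesthesia is not counted, because no irradiation follows it as RDT. Neoadjuvant RDT takes only the values 0 and 1. No row has a positive entry in both columns.

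**2. What the MTD definition returns**, reading it as the level below the one with two or more DLTs

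| Level with two or more DLTs | Level named as MTD | What that level contains |
|---|---|---|
| Cohort 1 | Cohort 0 | 1 adjuvant RDT fraction, no neoadjuvant RDT |
| Cohort 2 | Cohort 1 | 1 neoadjuvant RDT fraction, no adjuvant RDT |
| Cohort k, k = 3 to 8 | Cohort k-1 | k-1 adjuvant RDT fractions (2 to 7), no neoadjuvant RDT |
| None | Cohort 8 is the highest level tested | 8 adjuvant RDT fractions, no neoadjuvant RDT |

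If cohort 0 itself has two or more DLTs, no level lies below it.

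The cohort 2 row is the awkward one. A level with only neoadjuvant RDT is named because of DLTs at a level with only adjuvant RDT. By cohort number, the level below cohort 2 is cohort 1. By adjuvant fraction count, it is cohort 0.

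**3. Precision of the neoadjuvant evidence.** A cohort passes with 0/3 or 1/6. One-sided 95% upper limits for the DLT rate p (Clopper-Pearson):

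- 0/3: (1-p)^3 = 0.05, so p = 1 - 0.05^(1/3) = 0.632, or 63%.
- 1/6: (1-p)^6 + 6p(1-p)^5 = 0.05, so p = 0.582, or 58%.

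**4. Chance that cohort 1 passes.** With q = 1-p, P(pass) = q^3 + 3pq^2 × q^3.

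| True DLT rate | P(pass) |
|---|---|
| 10% | 0.729 + 0.243 × 0.729 = 0.91 |
| 20% | 0.512 + 0.384 × 0.512 = 0.71 |
| 33% | 0.301 + 0.444 × 0.301 = 0.43 |
| 50% | 0.125 + 0.375 × 0.125 = 0.17 |

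A pass is weak evidence of tolerability, and no later level adds neoadjuvant RDT data.

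**The case against.** The best reply is that the prefix in brackets is shorthand. There is one ladder and one MTD, the ladder includes cohorts 0 and 1, and the Abstract names the endpoint without the prefix. The neoadjuvant part has a disclosed role in histology and early safety. Table 2 defines every level, so a result at cohort 6 would visibly mean six adjuvant fractions. The objective also includes safety, which cohort 1 does address.

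Much of this stands. The document does not promise a separate neoadjuvant MTD, and nothing in it claims tolerability of combined use. But the endpoint section and the stated aim are broader than the Abstract, and the endpoint section is where the result takes its label. The disclosed role of the neoadjuvant part supports the narrower wording.

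Four stronger readings are not supported:

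- *Every stopping level is a number of adjuvant fractions.* This is false for a stop at cohort 2, where the rule names cohort 1.
- *Cohort 1 could show 0 DLTs in 6 patients, with an upper limit of 39%.* The stated rule expands a cohort only after a DLT, so the passing result with six patients is 1/6.
- *The wide limits are a defect peculiar to neoadjuvant RDT.* The 63% limit applies to any cohort of three without a DLT. What is peculiar here is that no other level bears on the neoadjuvant dose.
- *Tolerance differs because the adjuvant target is a post-operative cavity.* The document does not say this. It defines the gross tumour volume from contrast-enhancing tumour on pre- and postoperative MRI. The point rests on which levels are tested, not on biology.

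**Conclusion.** The point holds as a mismatch between the stated primary objective and the schedule. The ladder can support an MTD in number of adjuvant RDT fractions. For neoadjuvant RDT it gives a pass/fail check of one fraction in 3 patients (6 after a DLT), compatible with DLT rates up to 63% (0/3) or 58% (1/6). For neoadjuvant plus adjuvant RDT it gives no data.

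A reader might infer that the adjuvant MTD is itself invalid, or that the escalation must be redesigned. Neither follows from this point. The one place where the mismatch reaches the result itself is a stop at cohort 2.

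The conclusion assumes that Table 2 is the operative schedule. The trial design text says that the number of RDT fractions rises by one with each cohort, whereas Table 2 shows one fraction in total in both cohort 0 and cohort 1. It also assumes that the End-points definition means the level below the one with two or more DLTs, and that a cohort passes with 0/3 or 1/6.

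**What to change.** 1. In the End-points section and the trial design section, limit the MTD claim to the number of adjuvant RDT fractions, and align the Abstract with it.
2. Make the safety of cohort 1's single neoadjuvant RDT fraction a separate descriptive objective, with its own DLT count and confidence interval.
3. State that the MTD does not extend to neoadjuvant RDT or to RDT given both before and after surgery.
4. Reconcile the MTD definition and the trial design text with Table 2. Cohort 1 remains a level on the ladder but has no adjuvant RDT fraction, so the text must say how the result is reported and interpreted if escalation stops at cohort 2.

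The cost is a narrower claim and some redrafting. Treatment and patient numbers do not change. Item 4 is more than a wording change, because the scale on which the MTD is expressed has to be settled before the result is known.

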### Treatment procedures

#### Radiation treatment

The indication for second irradiation will be discussed and decided in the multidisciplinary tumor board before the screening process. Adjuvant radiotherapy will consist of fractioned photon irradiation, delivering a total dose of 36 Gy in 20 fractions, with five fractions applied per week (Monday through Friday). In cohorts 0 and 1, patients will receive two additional fractions of 1.8 Gy as neoadjuvant treatment, resulting in a cumulative dose of 39.6 Gy. Target definition and dose prescription will be according to ICRU 83 (for intensity-modulated radiotherapy) and planned with dedicated computed tomography (CT), pre- and postoperative contrast-enhanced MRI and three-dimensional planning systems. Gross tumor volume (GTV) will be defined in the pre- and postoperative MRI as the extend of the contrast-enhancing T1-hyperintense tumor site, the clinical target volume (CTV) will consist of a 1 cm margin around the GTV, also considering additional imaging (if available), respecting anatomical borders, and considering pre-treatment dose distributions. The planning target volume (PTV) will be defined as a 0.3–0.5 cm margin around the CTV. Dose constraints will be considered according to QUANTEC-recommendations. Intensity-modulated radiotherapy will be delivered with linear accelerators with a beam energy of 6 MV or 6 MV FFF, quality assurance will be performed by means of individual case reviews and image-guidance via frequent cone beam CT.

Preoperative irradiation will be performed in two fractions; one fraction daily, three and two days before the scheduled operative resection. Postoperative irradiation will begin after clinical recovery two to six weeks (as clinically indicated) after surgery.

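### The six-month OS, PFS and EFS rates run from study inclusion to a visit set six months after adjuvant radiotherapy begins, so they exceed six months and have different time origins in cohorts 0-1 and 2-8

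*Protocol article*

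**What the plan says.** The End-points section of the protocol article lists the secondary aims: "To evaluate six-months overall survival rate (OSR), six-months progression-free survival rate (PFSR) and six-months event-free survival rate (EFSR"). The next sentence fixes both ends of the window: "OSR, PFSR and EFSR will be determined from study inclusion to the second follow-up, six months after the beginning of adjuvant treatment".

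The Follow-Up section confirms the anchor of the second visit: "Additional follow-ups, including MRI-scans, will be performed twelve weeks and six months after the beginning of adjuvant treatment". Table 1 agrees.

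Table 1 has only one inclusion step, the screening visit with consent and eligibility check. Its timing depends on the cohort (the table puts a minus sign before the first number of each entry):
- Cohorts 0 and 1: "7 to -4 before surgery".
- Cohorts 2 to 8: "14 to -2 before first RDT". Table 2 places the first RDT on adjuvant day 1 in all of these cohorts.

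The Radiation treatment section gives the interval from surgery to adjuvant treatment: "Postoperative irradiation will begin after clinical recovery two to six weeks (as clinically indicated) after surgery". Only the first two cohorts are treated before surgery: "Additionally, in cohorts 0 and 1, patients will receive two neoadjuvant RT-fractions".

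The Statistical analysis section applies Kaplan-Meier, log-rank tests between subgroups and Cox regression to the survival endpoints, evaluates secondary endpoints by intention to treat, and compares all data with historical data.

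**The concern.** A six-month rate needs a stated origin and a fixed point six months later. Here the origin is inclusion, while the end is counted from a different and later date, the first adjuvant fraction. Three consequences follow.

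1. The rate is not a six-month rate in any cohort.
2. Time zero differs in kind. Cohorts 0-1 start before surgery and carry the risk of the operation and recovery. Cohorts 2-8 start only after surgery, when adjuvant radiotherapy is imminent.
3. A patient in cohorts 0-1 who dies before adjuvant radiotherapy has no date from which the end of the window can be set, yet intention to treat keeps that patient in the analysis.

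The trial has no concurrent control, so the survival rates will be interpreted largely against historical data. That comparison needs a rate of known length from a known origin. Pooled Kaplan-Meier, log-rank and Cox analyses counted from inclusion would also mix two origins.

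**Working it through.** **Inputs from the protocol article**
- Nominal length: 6 months (End-points).
- Screening to surgery, cohorts 0-1: 4 to 7 days (Table 1).
- Surgery to first adjuvant fraction: 2 to 6 weeks, that is 14 to 42 days (Radiation treatment).
- Screening to first RDT, cohorts 2-8: 2 to 14 days (Table 1); the first RDT is adjuvant day 1 (Table 2).
- Follow-Up 2: 6 months after the first adjuvant fraction (Table 1, Follow-Up, End-points).

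Assumption: study inclusion means the Table 1 screening step. One month = 30.44 days, so six months = 182.6 days.

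**Step 1. Lag from inclusion to first adjuvant fraction**
- Cohorts 0-1: 4 + 14 = 18 days to 7 + 42 = 49 days.
- Cohorts 2-8: 2 to 14 days.

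**Step 2. Window = 182.6 days + lag**

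| Cohorts | Window (days) | Window (months) | Excess over six months |
|---|---|---|---|
| 0-1 | 200.6 to 231.6 | 6.59 to 7.61 | 10% to 27% |
| 2-8 | 184.6 to 196.6 | 6.07 to 6.46 | 1% to 8% |

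The stated six months is not reproduced in either group, and the two ranges do not overlap.

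**Step 3. Is the origin before or after surgery?** Adjuvant radiotherapy starts at least 14 days after surgery, and screening in cohorts 2-8 is at most 14 days before it. Screening there cannot precede surgery. Table 1 agrees: the baseline MRI in cohorts 2-8 is the early postoperative scan, whereas cohorts 0-1 use the diagnostic scan.

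**Step 4. Effect on a rate read at Follow-Up 2.** The documents give no expected median, so this is an illustration. Assume a constant hazard and median PFS of 4 months: S(t) = exp(-ln 2 × t / 4).
- True six-month rate: S(6) = 35.4%.
- Cohorts 0-1: S(6.59) = 31.9% to S(7.61) = 26.7%.
- Cohorts 2-8: S(6.07) = 34.96% (35.0%) to S(6.46) = 32.6%.
- Smallest gap between groups: lags of 14 and 18 days, 32.65 - 31.91 = 0.7 points.
- Largest gap: lags of 2 and 49 days, 34.96 - 26.75 = 8.2 points.
- Mid-range lags of 8 and 33.5 days: 33.8 - 29.2 = 4.6 points.

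The result does not hinge on one assumed rate. Using S(6) raised to the power window/6, a true 50% reads 46.7% to 41.5% in cohorts 0-1 and 49.6% to 47.4% in cohorts 2-8. A true 30% reads 26.6% to 21.7% and 29.6% to 27.4%.

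**The case against.** The strongest reply is that the analysis method already protects the rate. Survival is to be analysed by Kaplan-Meier, and planned follow-up extends past six months from inclusion, so a true six-month rate from inclusion can be estimated. The End-points sentence could then be read as the observation period only. This is a possible reading, but the sentence says how the rates are determined and names the second follow-up as the end; no other landmark appears. It would also correct the length while leaving two time origins.

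A second reply is that a condensed article leaves such detail to the full protocol or SAP. That would excuse a missing definition. Here both ends of the window are given, and they do not match the label.

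Other parts of the opposing case stand and limit the point:
- **Size.** A reader might take about 8 points as the artefact. That is the corner case in which every cohort 0-1 patient waits 49 days and every cohort 2-8 patient 2 days. Cohorts 0-1 hold six patients unless expanded, so 8 points there is about half a patient (6 × 0.08 = 0.5).
- **Cohorts 2-8.** The excess may be only two days, and the illustrated shift is 0.4 to 2.7 points (35.36 - 34.96; 35.36 - 32.65).
- **Constant hazard.** For PFS it probably overstates the effect, because Table 1 schedules no study MRI between screening and week 12, so the extra early weeks may add few detected progressions.
- **Later cohorts looking better.** A reader might infer that later cohorts will appear superior for this reason alone. The documents do not support this: no survival comparison by cohort or number of RDT fractions is planned, only defined subgroups and risk factors such as age, KPS and gender.
- **Log-rank and Cox.** A reader might carry the downward bias over to these analyses. A longer window does not itself bias them. The mixed origin can, but its direction is uncertain, because the earlier start also gives cohorts 0-1 lead time.

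**Conclusion.** The endpoint definition is wrong as written: the stated rule does not deliver the stated six-month rate, its time zero differs between cohorts 0-1 and 2-8, and its end is undefined for cohort 0-1 patients who die before adjuvant radiotherapy. The window lengths rest on inclusion being the Table 1 screening step, which is the only inclusion step described. The percentages rest additionally on the assumed hazard and median, and apply only to a rate read at Follow-Up 2.

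The practical weight is moderate. These are secondary endpoints in a dose-escalation trial; neither the MTD nor an escalation decision depends on them. The material discrepancy, 18 to 49 days, is confined to cohorts 0-1. It counts chiefly in the comparison with historical data and in pooled survival analyses.

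**What to change.** Amend the End-points sentence to state one time origin and one fixed six-month Kaplan-Meier landmark for all cohorts. One workable version:

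- Count from the first adjuvant fraction, to which Follow-Up 2 is already tied.
- For PFSR and EFSR, let the landmark include the Follow-Up 2 visit window. A hard cut at 182 days would classify a progression found on a slightly late scan as progression-free at six months.
- Count deaths, progressions and other endpoint events between inclusion and day 1 as failures in the intention-to-treat rate, and also list them separately. Merely moving the origin to day 1 would drop these events from the main estimate and condition on reaching adjuvant radiotherapy. That would conflict with the intention-to-treat rule, and cohort 1's only RDT fraction falls on day -3, before that origin.
- Show cohorts 0-1 and 2-8 separately as well as pooled.
- Give the six-month rate from inclusion as a sensitivity analysis.

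The cost is one amended sentence and one extra analysis. The dates needed are those of scheduled trial steps, and no treatment or visit changes. The small downside is that pre-adjuvant events in cohorts 0-1 slightly lower the rate.
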